# Culturally adapted motivational interviewing with cognitive behavior therapy and mindfulness-based relapse prevention for substance use disorder in Pakistan (CAMAIB): protocol for a feasibility factorial randomised controlled trial

**DOI:** 10.1186/s40814-023-01296-0

**Published:** 2023-04-24

**Keywords:** Cognitive behavioral therapy, Motivational interviewing, Mindfulness-based relapse prevention, Substance use disorder, Pakistan

## Abstract

**Background:**

The use of psychoactive substances significantly impacts the health, social and economic aspects of families, communities and nations. There is a need to develop and test psychological interventions aimed for individuals with substance use disorder (SUD) in lower- and middle-income countries (LMICs), such as in Pakistan. The aim of this exploratory trial is to test the feasibility and acceptability of two culturally adapted psychological interventions in a factorial randomised controlled trial (RCT).

**Methods:**

The proposed project will be conducted in three phases. The first phase of the study will focus on cultural adaptation of the interventions through qualitative interviews with key stakeholders. The second phase will be to refine and produce manually assisted interventions. Third and last stage would be to assess the feasibility of the culturally adapted interventions through a factorial RCT. The study will be carried out in Karachi, Hyderabad, Peshawar, Lahore and Rawalpindi, Pakistan. Recruitment of participants will take place from primary care and volunteer organisations/drug rehabilitation centres. A total of 260 individuals diagnosed with SUD (*n* = 65) in each of the four arms will be recruited. The intervention will be delivered weekly over a period of 12 weeks in both individual and group settings. Assessments will be carried out at baseline, at 12th week (after completion of intervention) and 24th week post-randomisation. The analysis will determine the feasibility of recruitment, randomisation, retention and intervention delivery. Acceptability of intervention will be determined in terms of adherence to intervention, i.e. the mean number of sessions attended, number of home assignments completed, attrition rates, as well as through process evaluation to understand the implementation process, context, participants’ satisfaction, and impact of the study intervention. The health resource use and impact on the quality of life will be established through health economic data.

**Discussion:**

This study will provide evidence for feasibility and acceptability of culturally adapted manually assisted psychological interventions for individuals with SUD in the context of Pakistan. The study will have clinical implications if intervention is proven feasible and acceptable.

**Trial registration:**

Name of the registry: ClinicalTrials.gov, Trial registration number: NCT04885569, Date of registration: 25th April 2021.

**Supplementary Information:**

The online version contains supplementary material available at 10.1186/s40814-023-01296-0.

## Background

The use of psychoactive substances significantly impacts the health, social and economic aspects of families, communities and nations. In 2019, approximately 275 million people worldwide used illicit substances with almost half a million deaths related to substance misuse [1]. Substance misuse has resulted in 18 million years of healthy life lost [1]. Substance misuse has increased 22 percent in last 10 years and it is thought that the number of people using illicit substance will increase further 11% by 2030 [1]. According to the World Drug Report [2], only 1 out of 8 people receive the required treatment for substance misuse. In Pakistan, 7.6 million people use illicit substances and approximately 4.25 million people are dependent [3] with 50,000 more people becoming dependent on illicit substances each year [4]. This calls for urgent attention and treatment approaches for individuals with SUD [3]. In Pakistan, there is a higher prevalence of substance misuse amongst men compared to women [5]. Amongst men, cannabis and opioids have been the most used substances [5]. Heroin is consumed more in Pakistan than in any other country in the South Asian region [5]. In women, there is a higher prevalence of prescription opioids, tranquilizers and sedatives misuse [3].

Previous history of substance use, lack of family support and stress have been reported as underpinned associations of relapse [6]. Though there are strong religious and cultural objections to substance use, it is a highly prevalent problem amongst the youth of Pakistan. These findings suggest an increased burden on public health resources. The majority of people who use illicit substances belong to the poor strata of the society [3]. With most detoxification centres in Pakistan being operated by non-governmental organizations (NGOs), access to treatment is limited. Around 75% of people dependent on opiates are left without an avenue to seek help (Bureau of International Narcotics and Law Enforcement Affairs [7]. It is therefore necessary to address needs of this population in order to provide effective and targeted interventions.

Evidence suggests that psychological interventions such as Cognitive Behavioural Therapy (CBT), Motivational Interviewing (MI) and Relapse Prevention (RP) interventions are effective treatments for substance misuse [8]. CBT is considered as the most effective psychological treatment for SUD [9, 10]. The CBT approach comprises of different types of interventions [11] such as CBT based MI [12], mindfulness based stress reduction [13], Mindfulness-Based Relapse Prevention (MBRP) [14] which can either be combined or used as standalone interventions. Although, CBT focuses on unpleasant or distressing events, thoughts and actions, different approaches of CBT may aim to reduce the impact of internal triggers and promote coping skills to maintain abstinence in the long term [15]. For example, CBT-based MI (MICBT) for substance misuse focus on improving motivation to change (to improve access and engagement with the services) and on prevention of relapse. MI is effective in improving motivation to change [16] and to produce significant change in multiple substance related outcomes [17–19]. The addition of MI assessment has been shown to increase engagement and adherence to overall treatment [20].

In addition to MICBT, RP is another commonly used CBT intervention for SUDs developed to help clients maintain abstinence by identifying internal and external triggers and promoting effective coping skills that increase self-efficacy in managing triggers and reduce the risk of relapse [20]. Furthermore, MBRP is an extension of CBT-based RP approach that focuses on identifying triggers, thoughts and cravings, automatic reactions to those triggers, and using mindfulness as a way of effectively coping with situations that may trigger relapse [21, 22]. Mindfulness-based interventions have been increasingly developed and evaluated for the treatment of SUD [23]. Although, CBT and its different approaches, i.e., MICBT and MBRP have shown to be effective interventions for substance misuse, these are widely used in high-income countries [24] and there is high degree of heterogeneity as reported in a previous systematic review [25]. So, the evidence of the efficacy of MICBT and MBRP for SUD in LMICs is scarce. There is also an identified need to culturally adapt CBT for LMICs [10]. In Pakistan, there has been very little research in this area.

## Study aims and objectives

The study aims to culturally adapt and integrate two CBT approaches, MICBT and MBRP intervention for individuals with SUDs in Pakistan and to test the feasibility and acceptability of these interventions in a factorial RCT.

## Methods

### Study design and setting

This will be a four-arm feasibility factorial RCT. An overview of complete study design is provided in Fig. 1. The proposed project will consist of three phases. The first phase of the study will focus on the adaptation/development of the intervention in accordance with the Pakistani culture. The second phase will include refinement of the interventions and production of the intervention manuals. The third phase will be to assess the feasibility through a factorial RCT. The study will be carried out in Karachi, Hyderabad, Peshawar, Lahore and Rawalpindi, Pakistan. Recruitment of participants will be from primary care and volunteer organisations/drug rehabilitation centres.

**Fig. 1 Fig1:**
[figure not shown]
Flow diagram describing the timeline of study procedures

### Phase 1: intervention adaptation/development

The first stage of the study will comprise of focus groups and in-depth interviews with service users and other stakeholders. The purpose of this phase is the cultural adaptation of the evidence-based MICBT [12, 26, 27] and MBRP [28, 29] for the study population. Through qualitative work, the culturally adapted intervention will be developed for people with SUD, as well as an accompanying manual. Focus groups will be conducted with key stakeholder groups including (1) service users, (2) family members/carers, (3) health professionals and (4) Community leaders, religious scholars (Imams) (8–10 in each group; total sample *n* = 32–40). We will also conduct 1:1 individual interviews if participant is not willing for focus group discussion.

There will be active selection of participants in order to represent the wider population. Focus group interviews will be conducted by a trained research assistant, lasting between 60 and 90 min—including the time for setting up and addressing participants’ queries. The topic guide will be developed in collaboration with the members from the service user and carer’s advisory group. For consistency, the same topic guide will be used with participants who prefer individual interviews. Data will be analysed using thematic analysis [30] for emergent themes relevant to the cultural adaptation of MICBT and MBRP. The following areas will be considered specifically (1) experiences with the services, (2) opinions on the cultural adaptation of MICBT and MBRP intervention, (3) identifying and understanding barriers limiting access to services, and (4) opinions on how best to involve family in the treatment plan. Our group has culturally adapted interventions for a range of mental disorders using mixed methods in Pakistan and the UK and we will follow same procedures described elsewhere [31–39].

### Phase 2: test run and intervention refinement

Phase 2 will involve preliminary testing of the culturally adapted intervention in a small group of participants. Cultural adaptation of the intervention requires an understanding of the religious and socio-cultural constructs of the population. This will take into consideration the explanatory models of any illness, along with understanding of underlying beliefs and values [31]. Such adaptations are reported to increase the acceptability and uptake of psychological and social interventions. Once the cultural adaptation is complete, a sample of 12 participants diagnosed with SUD will be invited to participate in the test run of the intervention. This will consist of 8 individual and 4 group sessions focusing on distinct yet related stages: exploring motivation to change; exploring the process of change; identifying strategies to consolidate commitment to change, explore effective coping skills, increase awareness and development of flexible responding in the presence of triggers of relapse. Feedback will be gathered from the participants, therapists and staff, on the relevance and acceptability of the culturally adapted interventions. All participants of trial run will be invited to be interviewed to explore their opinions on intervention relevance and acceptability. All interviews will be carried out by researchers from outside the local community in order to further protect interviewee confidentiality. These interviews will be recorded and transcribed. The interview guide will include some predetermined questions (based on findings from phase 1) and some open-ended questions to facilitate emergence of new themes.

### Phase 3: feasibility factorial RCT

The feasibility of the intervention will be assessed using a factorial RCT, for MICBT and MBRP intervention, comparing four groups: (1) MICBT plus treatment as usual group (TAU), (2) MBRP plus TAU group, (3) the integrated MICBT and MBRP with TAU and (4) TAU group alone. In Pakistani culture, people consider themselves more as part of a family and larger community rather than as individuals. Therefore, a group approach is more culturally appropriate but for certain private/family issues the flexibility of some individual time with the therapists will be offered. The group sessions will consist of approximately eight participants.

### Eligibility criteria

Participants meeting DSM-V criteria for SUD, aged 18 years and above, understand spoken Urdu and have completed the detoxification process (to ensure engagement in the intervention) will be included. Exclusions will be made if there will be any evidence of organic brain disease, clinically significant co-occurring medical illness or mental illness to the extent that can prevent participation in the intervention. A trained research assistant (RA) will confirm participants’ eligibility against inclusion/exclusion criteria and obtain informed consent.

### Interventions

#### Explanation for the choice of comparators

MI is being increasingly blended with treatments such as CBT to enhance intrinsic motivation for behavioural change and found to have positive outcomes [40]; however, further research is required to replicate these findings in LMICs such as Pakistan. Similarly, a recent review of 54 RCTs supports efficacy of mindfulness-based interventions for SUDs and RP [29]. However, the review also calls for more rigorous research designs with longer follow-up periods [29]. The review concluded that the most effective intervention approach to target SUD is to combine mindfulness interventions with treatment-as-usual (TAU) or other active treatments. Another review by Garland and Howard [41] has also provided strong recommendations for the next wave of research to firmly establish the efficacy of mindfulness interventions for SUD.

### Intervention description

#### CBT-based Motivational Interviewing (MICBT)

The culturally adapted MICBT [26, 27] includes approaches of CBT based motivational interviewing. MI is a well-developed intervention for exploring and resolving the ambivalence to change behaviour. MICBT [27] includes techniques to increase and consolidate motivation to make positive changes in individuals with problematic substance use, cognitive restructuring, learning assertiveness and problem solving skills combined with cognitive behavioural relapse prevention approaches. The cognitive behavioural model of substance use suggests that problematic substance use is maintained by thoughts of reduced ability to cope when faced with high-risk situations. Beliefs regarding inability to cope with difficulties interact with physiological cravings and psychological urges to use. During this time, the decision to use or continue to use substances is made. Relief from cravings and urges occur and reinforce the belief that substance use is the only way to manage such situations. This intervention will focus on ambivalence to change substance use behaviour. This will also identify and help solve difficulties in changing substance use behaviour by offering ways of managing these difficulties through CBT.

#### Mindfulness based Relapse Prevention (MBRP)

MBRP [28] incorporates mindfulness-based practices with cognitive-behavioural skills to reduce likelihood of relapse, increase awareness and flexible responding towards triggers of SUD. Rationale of MBRP practices is its explicit emphasis to increase awareness to external triggers and discrete emotional, behavioural and cognitive reaction patterns are focused during initial sessions of intervention [28]. Exercises and practices explore the functions of habitual behaviours such as substance misuse and focus on the balance between acceptance of present moment and skilful action to bring real change. Moreover, MBRP put emphasis on association of thought content and relapse cycle and encouraged to focus on thoughts simply as thoughts and not essentially as reality. The latter sessions of MBRP centre on sustainability of learned skills in daily life, and to identifying or establish access to resources to strengthen supportive social networks [28].

#### CAMIAB intervention

This will be MICBT integrated with MBRP intervention. The interventions will be manualised and will include both individual as well as group sessions.

#### Treatment As Usual (TAU)

We will carefully record the routine care treatment that the participants will be receiving.

The intervention will be delivered alongside TAU in all study arms and participants will not be asked to cease any practices that they are currently undertaking on either control or intervention arm. Existing services received will be monitored and recorded throughout the trial. Intervention sessions will be delivered according to adapted intervention manuals. Manually assisted interventions help standardise the intervention in different settings and benefit in monitoring intervention fidelity.

### Criteria for discontinuing or modifying allocated interventions

The study interventions outlined are not expected to cause any adverse effects nor there is any anticipated harm to come from study participation. However, participants will be free to withdraw from the study at any point. The intervention will be discontinued if any individual participant requests to withdraw from the study or if any adverse effects warrant terminating the intervention. Given that this is a feasibility study, there will be no modifications in allocated treatments but a process evaluation will be undertaken to refine the intervention for a future definitive trial. After completion of intervention session, participants in need of further clinical interventions or who have not responded to intervention and those in TAU group will be referred to appropriate services.

### Strategies to improve adherence to interventions

Intervention sessions will be delivered according to adapted manuals and the intervention adherence will be monitored by number of sessions attended. The intervention will be delivered by trained therapist in supervision of senior therapist who have training and experience in conducting psychological interventions for SUD.

### Outcomes

#### Primary outcomes: feasibility indicators

Feasibility will be determined by following indicators:Recruitment rates, attendance (number of sessions attended), retention rate and randomisation.Acceptability of interventions based on client satisfaction, adherence rate (the number of sessions attended, number of home assignments completed) and attrition rates.Completeness of assessment by participants.

Meeting the progression criteria of > 50% of recruitment, > 70% of retention, > 60% of attendance, > 70% of adherence, < 30% of attrition and > 70% of assessment completion at study end will determine that a full definitive trial is needed.

#### Secondary outcomes

*The Maudsley Addiction Profile (MAP)* [42] is a brief questionnaire to measure problems in four domains that include substance use, health risk behaviour, physical and psychological health, and personal/social functions.

*The Short Warwick-Edinburgh Mental Well-being Scale (SWEMWBS)* [42] will be used to measure mental wellbeing. It consists of 7 statements on a 5-point Likert scale. The minimum scale score is 7 and the maximum is 35. The high score indicates better mental wellbeing.

*Quality of Life* [43] This will be measured using EuroQoL (EQ-5D) a standardised instrument to measure health outcomes and quality of life.

*Client Service Receipt Inventory (CSRI)* [44] will be used to estimate the health and social services received.

### Study procedure

The study procedure is outlined in Fig. 1 and in the Standard Protocol Items: Recommendations for Interventional Trials (SPIRIT) diagram (Table 1). A completed SPIRIT checklist is given as Additional file 1.

**Table 1 Tab1:**
[figure not shown]
Standard Protocol Items: Recommendations for Interventional Trials (SPIRIT) diagram

Schedule of enrolment, interventions and assessments

#### Sample size

Based on the recommendations by Sim and Lewis [45], a minimum sample size of at least 50 participants per group is required for feasibility studies. Assuming 30% attrition rate, we aim to recruit a total of *N* = 260 participants, with 65 participants randomised to each arm according to 2 × 2 factorial design scheduled in given Table 2.

**Table 2 Tab2:** 2 × 2 Factorial design schedule of intervention with sample size

	TAU	MBRP	Total
MICBT	65	65	130
TAU	65	65	130
Total	130	130	260

The findings of this feasibility study will help determine the initial data for the outcome measures and will help in providing a sample size estimate for a larger future definitive trial; therefore, no formal power calculations have been undertaken.

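### At the plan's own 30% attrition, 65 per arm leaves about 45 to 46, short of its stated minimum of 50 per group

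*Protocol article*

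**What the plan says.** The Sample size section of the protocol article builds the target in two steps. It first cites a rule of thumb: "a minimum sample size of at least 50 participants per group is required for feasibility studies". It then continues "Assuming 30% attrition rate, we aim to recruit a total of" 260, "with 65 participants randomised to each arm according to 2 × 2 factorial design". Table 2 shows 65 in each cell of the 2 × 2 layout, and the Methods part of the abstract repeats 260 and 65 per arm. The section adds that "no formal power calculations have been undertaken", so the rule of thumb and the attrition allowance are the only stated basis for the number.

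The section on primary outcomes (feasibility indicators) sets progression limits that include retention above 70% and "> 70% of adherence, < 30% of attrition and > 70% of assessment completion at study end".

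**The concern.** An attrition allowance exists so that the required number is still there after losses. The section moves from 50 to 65 by way of the 30% assumption alone, so 50 reads as the number to be retained. Yet 30% of 65 is 19.5, and 65 less 19.5 is below 50. The value 65 is what results from adding 30% to 50, a common slip, when the allowance should be obtained by dividing 50 by the fraction retained.

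At stake is whether the sole justification for the sample size is true as written. The retained sample is what the plan uses for confidence intervals on group differences (Statistical analysis), for effect sizes to power a later trial (Statistical methods to handle missing data) and for the future sample size estimate (Sample size). An uncorrected allowance could also be carried into the definitive trial.

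**Working it through.** **Inputs, all from the protocol article**
- Minimum per group, m = 50 (Sample size)
- Attrition, d = 0.30 (Sample size)
- Randomised per arm, n = 65; four arms; total 260 (Sample size, Table 2, abstract)
- Progression limits: attrition below 30%, retention above 70% (Primary outcomes: feasibility indicators)

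**1. Reproducing the stated figure**
- m × (1 + d) = 50 × 1.30 = 65 per arm; 65 × 4 = 260. This matches exactly.
- m / (1 − d) = 50 / 0.70 = 71.4, rounded up to 72 per arm; 72 × 4 = 288. This does not match.
- Inflating the total once: 200 / 0.70 = 285.7, rounded up to 286. This does not match either.

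The formula is inferred from the match. The next step does not depend on it.

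**2. What 65 per arm leaves at 30% attrition**
- Per arm: 65 × 0.70 = 45.5
- Total: 260 × 0.70 = 182
- Shortfall: 50 − 45.5 = 4.5 per arm, or 4.5 / 50 = 9%; in total 200 − 182 = 18

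**3. Attrition at which 65 per arm still gives 50**
- 1 − 50/65 = 0.231, i.e. at most 15 losses per arm, or about 23%

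**4. Overlap with the progression limits**

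Taken over the whole trial:
- 60 losses leave exactly 200 (60/260 = 23.1%).
- 61 losses (23.5%) leave 199, and 77 losses (29.6%) leave 183.
- Any number of losses from 61 to 77 keeps attrition below 30% and retention above 70%, yet leaves fewer than 50 per arm on average.

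**5. Size of the consequence**
- Confidence intervals for differences in means between arms scale with 1/√n. The ratio is √(50 / 45.5) = 1.048, so about 5% wider.
- The approximate relative standard error of an SD, 1/√(2(n − 1)), is 1/√98 = 10.1% with 50 and 1/√89 = 10.6% with 45.5.
- Retention and attrition are proportions of those randomised. Their denominator stays 65 per arm (260) however many are lost.

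**6. Check of the corrected number**
- 72 × 0.70 = 50.4 per arm, at or above 50 in expectation. It needs 7 more per arm and 28 more in total.

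**The case against.** The strongest defence is that little depends on this. The trial is a feasibility study with a largely descriptive analysis and no power claim. Progression rests on feasibility percentages, none of which requires 50 completers per arm. All of that stands and limits the weight of the point. It does not make the figures agree: with no power calculation, the 50-per-group rule is the only support for 260, and 260 does not meet it under the stated attrition.

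Two other readings could rescue the number.
- **The 50 might apply before attrition.** Then no allowance would be needed and 50 per arm would suffice; the step to 65 would have no purpose.
- **Group might mean a factorial margin,** where 130 × 0.70 = 91 remain. But the section on the factorial RCT (Phase 3) counts four groups and lists the four arms, and the Sample size section goes straight from 50 per group to 65 per arm.

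A reader might also infer more than the document supports.
- **That precision is overstated, including that of the retention rate.** The article prints no precision figure, and the precision of the retention rate does not depend on how many complete.
- **That the article states the 1.3 multiplier, or says in terms that 50 will remain.** It does neither. The first is a match of figures. The second is the natural meaning of an attrition allowance.
- **That the design or the progression decision is undermined.** A shortfall of 4 to 5 people per arm in follow-up data does not do that.

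**Conclusion.** The point holds in a limited form: the Sample size section is inconsistent as written. At its own 30% attrition, 65 per arm leaves about 45 to 46 (182 in total), 9% below its own minimum. The minimum is reached only if attrition is at most about 23%. Attrition between that value and 30% would pass the attrition and retention criteria and still fall short.

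The practical effect is modest, with intervals about 5% wider for group differences on follow-up measures and no effect on the precision of the retention rate. It should be fixed, but it does not threaten the trial.

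The conclusion assumes that 50 is meant as a number retained in each of the four arms, and that losses are similar across arms. The section does not say at which visit the 30% applies, so the figures refer to follow-up data in general.

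**What to change.** Keep 260 and reword both sentences of the justification. Adding the expected number while leaving 50 as a requirement would make the protocol openly miss its own minimum. Suggested sense:

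*We aim for 50 participants per arm with follow-up data. Randomising 65 per arm (260 in total) reaches this target if attrition is at most 23%. At 30% attrition, about 45 to 46 per arm (182 in total) are expected to provide follow-up data.*

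This costs two sentences and no extra participants; the stated retained number becomes slightly less favourable.

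If the sponsor wants both 50 retained per arm and an allowance for 30% attrition, the consistent target is 72 per arm and 288 in total, which is 28 more participants. Table 2 and the abstract would then change as well. The Trial status section says recruitment had not begun, so on the article's own account either route was open.
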